Bi-weekly phone calls will be made by the research team to parents to enquire about any gastrointestinal adverse effects, such as the number of stools per day, difficulty in passing stool as the number of stools difficult to pass per day, and stool consistency recorded using a validated 5-point scale (1 = watery, 2 = runny, 3 = mushy soft, 4 = formed, and 5 = hard) provided in a pictorial representation to parents. The frequency of spitting-up/vomiting and flatulence episodes per day will be recorded on a categorical scale (1 time; 2–3 times; 4–6 times; >7 times). Categorical scales will also be used to assess the daily durations of crying or fussing (<10 min; 10–30 min; >30 min to 1 h; >1–2 h; >2–3 h; >3 h), sleeping (0–7, 8–12, 12–16, 16–20, 20–24 h), or the severity of spitting-up/vomiting (1 teaspoon or less; 1 tablespoon; 2 tablespoons; about half of the feeding; more than half of the feeding). Episodes of abdominal distension (present or absent) shall be recorded in a parent diary. All adverse events will be recorded and evaluated by the investigators for causality and severity. Adverse events will be considered as serious if they are life-threatening, cause permanent harm, or results in hospitalization. All other adverse events will be considered non-serious.

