### 2.17. Probiotic Protocol

Enrolled neonates will be supplemented with the freshly reconstituted contents of the allocated sachets every day, which will be continued till four months of age. The dry, lyophilized powder in the sachets will be reconstituted using the mums’ own milk (first choice) or sterile water for injection. The dose will be 3 × 10^9^ CFU/day (1 mL reconstituted solution twice daily). Supplementation will be temporarily withheld if vomiting, diarrhea, or abdominal distension is noted.

The manufacturer, Morinaga Milk Industry Co., Ltd., are not a sponsor and will only supply the probiotic and placebo free for the trial and are not involved in the design, conduct, analysis, and reporting of the trial.

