### 3.7. Statistical Analysis of Clinical, SCFA, Bile Acid and Microbiome Data

Analysis will be based on the intention-to-treat principle. The continuous data will be summarized using median, interquartile range, and range. The categorical data will be summarized using frequency distributions. Univariate comparisons for the continuous data will be made using the Mann–Whitney test. For the categorical data, the Chi-square or Fisher exact test will be used.

The SCFA data will be analysed using a linear mixed model effect (LME) test to assess the differences between the groups over time. In this analysis, the subjects will be modelled as a random factor, and time and treatment are fixed factors. All the tests will be two-sided, and a *p*-value < 0.05 will be considered significant. The data on clinical outcomes will be analysed using SPSS version 22.0 statistical software (Armonk, NY, USA: IBM Corp.) and SCFA in R (version 3.5.1).

**Pre-planned subgroups:** (1) Infants who are born through caesarean section due to increased risk of gut dysbiosis. (2) Infants born to mothers with diet-controlled vs. insulin-dependent GDM. (3) Infants born to mothers with GDM and a normal vs. high BMI.

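### Low weight: if the arms are compared on the ordered vomiting, flatulence and crying scales, the Chi-square/Fisher rule in 3.7 ignores the order of the levels and gives up power

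*Protocol article*

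**What the plan says.** Section 2.14 (Safety Monitoring) sets the data collection: "Bi-weekly phone calls will be made by the research team to parents". On these calls, "The frequency of spitting-up/vomiting and flatulence episodes per day will be recorded on a categorical scale", with four levels. The section continues: "Categorical scales will also be used to assess the daily durations of crying or fussing", with six levels from under 10 minutes to over 3 hours. The same sentence covers "the severity of spitting-up/vomiting (1 teaspoon or less; 1 tablespoon; 2 tablespoons; about half of the feeding; more than half of the feeding", which has five levels, and sleep duration, which also has five.

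Section 3.7 gives one general rule for each type of data. Continuous data are compared with the Mann-Whitney test. For the rest, "For the categorical data, the Chi-square or Fisher exact test will be used". Tests are two-sided at 0.05. Ordered categories get no rule of their own.

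The article does not say that the arms will be compared on these scales, or how the repeated reports would be reduced to one value per infant. Sections 2.10 and 2.11 do not list them as outcomes.

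**The concern.** Chi-square and Fisher's exact test treat the levels as unordered labels: shuffle the columns of the table and the p-value is unchanged. On a scale running from one episode a day to more than seven, the likely sign of poor tolerance is a graded shift towards the higher levels. A test that ignores order spreads its power over every possible pattern of difference, so it detects that shift less often than a rank test does.

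Because 2.14 labels the scales categorical, a literal reading of 3.7 sends them to the less sensitive test, although the more suitable one is named in the same paragraph. With 30 infants per arm there is little power to spare, and in a tolerability comparison a missed shift reads as no difference.

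**Working it through.** **Inputs from the article.** 30 infants per arm (2.9); two-sided 0.05 (3.7); 4 levels for vomiting and flatulence frequency, 5 for vomiting severity, 6 for crying or fussing (2.14). The article gives no expected distribution, effect or power for these scales, so there is no figure of its own to reproduce.

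**Assumptions.** One level per infant; a proportional-odds shift between arms; control distributions that are even, middle-peaked, skewed or heavily concentrated in the lowest level; odds ratios from 1.5 to 4.

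**Step 1: one table by hand.** Hypothetical counts on a 4-level scale: 14/9/5/2 against 7/8/9/6.

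- *Chi-square.* Column totals are 21, 17, 14 and 8, so the expected counts per arm are 10.5, 8.5, 7 and 4. The statistic is 2 × (3.5²/10.5 + 0.5²/8.5 + 2²/7 + 2²/4) = 2 × (1.167 + 0.029 + 0.571 + 1.000) = 5.53 on 3 degrees of freedom, p = 0.137. Fisher gives p = 0.152.
- *Mann-Whitney.* The mid-ranks are 11, 30, 45.5 and 56.5. The first arm's rank sum is 14×11 + 9×30 + 5×45.5 + 2×56.5 = 764.5, against 30×61/2 = 915 expected. The tie term is (9240 + 4896 + 2730 + 504)/(60×59) = 17370/3540 = 4.907. The variance is (30×30/12) × (61 − 4.907) = 4207, so the SD is 64.9. Then z = 150.5/64.9 = 2.32, p = 0.020 (0.021 with a continuity correction).

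The table shows the mechanism only. The counts are invented and fall either side of 0.05.

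**Step 2: power by simulation.** Pearson Chi-square, exact Fisher (Freeman-Halton) and tie-corrected Mann-Whitney, 30 per arm. Chi-square and Mann-Whitney rest on 8,000 trials per row. Fisher rests on 1,500 (4 and 5 levels) or 600 (6 levels), so its standard error is up to about √(0.4×0.6/600) = 2 points.

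| Control distribution | Odds ratio | Chi-square | Fisher | Mann-Whitney | Loss, Chi-square / Fisher (points) |
|---|---|---|---|---|---|
| 4 levels, even | 2 | 0.205 | 0.202 | 0.307 | 10.2 / 10.5 |
| | 3 | 0.464 | 0.442 | 0.639 | 17.6 / 19.7 |
| | 4 | 0.671 | 0.658 | 0.822 | 15.1 / 16.4 |
| 4 levels (.70, .20, .07, .03) | 2 | 0.152 | 0.188 | 0.260 | 10.8 / 7.2 |
| | 3 | 0.385 | 0.407 | 0.570 | 18.5 / 16.3 |
| | 4 | 0.602 | 0.640 | 0.774 | 17.2 / 13.4 |
| 5 levels, even | 2 | 0.175 | 0.179 | 0.318 | 14.3 / 13.9 |
| | 3 | 0.415 | 0.407 | 0.648 | 23.2 / 24.1 |
| | 4 | 0.618 | 0.643 | 0.841 | 22.3 / 19.9 |
| 6 levels (.35, .25, .18, .12, .07, .03) | 2 | 0.141 | 0.168 | 0.312 | 17.1 / 14.3 |
| | 3 | 0.374 | 0.403 | 0.654 | 28.0 / 25.1 |
| | 4 | 0.579 | 0.590 | 0.849 | 27.1 / 25.9 |

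The loss grows with the number of levels. Across all distributions tried it is about 10-17 points (Chi-square) and 7-19 (Fisher) at odds ratio 2, and about 15-30 and 13-27 at odds ratio 3-4. One extreme 6-level distribution, with 80% in the lowest level, reached 32 for Chi-square at odds ratio 4. At odds ratio 1.5 the loss is 4-7 and 3-5 points, and Mann-Whitney itself has only 10-14% power.

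**Step 3: no effect.** Rejection rates at odds ratio 1 stay at or below about 5% for all three tests, within simulation error. The planned tests are valid, and the rank test's gain does not come from extra false positives.

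**Step 4: sleep.** For sleep duration a change in both directions is plausible, with more short and more long sleepers. With assumed proportions (.02, .13, .45, .35, .05) against (.12, .23, .20, .25, .20), Chi-square has about 67% power and Mann-Whitney about 7%. The advantage reverses, so sleep does not belong in this point.

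**The case against.** The strongest reply is that the article makes no error here. No between-arm test of these scales is announced; they are collected under safety monitoring and are not outcomes. The stated safety handling does not use them: "All adverse events will be recorded and evaluated by the investigators for causality and severity", "Supplementation will be temporarily withheld if vomiting, diarrhea, or abdominal distension is noted", and the monitoring committee reviews serious events. The point also needs a chain of conditions: the arms are compared, repeated reports become one ordered level per infant, and that level is tested as 3.7 literally says. If the reports were averaged to a score, Mann-Whitney would already apply; if reduced to yes/no, Chi-square or Fisher would be right. A separate analysis plan could settle all of this.

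Most of that stands, and it sets the weight. It does not remove the point, because 3.7 is not silent: it states a rule, and the article's own label places these scales under it.

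Three stronger readings are tempting and not supported:

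- *That the trial plans a faulty safety analysis.* The article commits to no such analysis, and safety decisions do not rest on these scales.
- *That 15-30 points of power will be lost.* That range needs assumed odds ratios of 3-4. At odds ratio 2 Mann-Whitney itself reaches only about 21-32%, so for modest effects the main limit is 30 infants per arm.
- *That every ordered scale in 2.14 should go to Mann-Whitney.* The sleep example shows otherwise.

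**Conclusion.** The point holds as an optional improvement. The rule in 3.7, applied to the vomiting, flatulence and crying scales with one level per infant, would discard their order. The cost is about 10-17 points of power with Chi-square and 7-19 with Fisher at odds ratio 2, about 15-30 and 13-27 at odds ratio 3-4, and a few points at odds ratio 1.5.

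These sizes rest on assumed control distributions, an assumed proportional-odds shift and 30 scored infants per arm. The last is itself uncertain: the frequency scale starts at one episode and the severity scale at a teaspoon or less, so neither has a printed level for an infant with no episode. Error rates and the primary and secondary outcomes are not affected.

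**What to change.** In 3.7, limit the Chi-square/Fisher rule to unordered or yes/no data, and add a sentence such as: *If the arms are compared on vomiting or flatulence frequency, vomiting severity or crying duration, each infant's summary level over the supplementation period will be compared with the Mann-Whitney test; infants with no episode are placed in a lowest level, none.* Name the summary level, for example the worst reported.

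Keep sleep duration out of this rule, or show its full distribution by arm.

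The cost is one or two sentences in 3.7 or the analysis plan, with no new data, visits or staff. There are two small drawbacks. Mann-Whitney is less sensitive to differences that do not run in one direction. A worst level also tends to rise with the number of reports, so the number of calls completed should be shown for each arm.

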### 2.7. Intervention

Triple-strain Bifidobacteria: 1 × 10^9^ CFU of each (*Bifidobacterium breve* M-16V, *Bifidobacterium longum* subsp. *infantis* M-63, *Bifidobacterium longum* subsp. *longum* BB536) administered from birth till 4 months of age.

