### 2.9. Sample Size Calculation

A sample size of 30 per group (total 60) was considered adequate to detect a 1.5-fold difference in alpha diversity with 80% power and a significance level of 0.05. By focusing on biological relevance, this sample size ensures that even subtle changes in microbial composition can be detected, providing a robust foundation for understanding the underlying biological mechanisms. This sample size allows for the detection of biologically meaningful variations in microbial composition, ensuring that differences in diversity metrics, such as Shannon diversity or Bray–Curtis dissimilarity, are statistically significant. By focusing on these well-defined biological parameters, this study can reliably capture important variations in microbial communities, providing a strong foundation for understanding their role in the system under investigation [21,22,23].

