### 2.11. Secondary Outcomes

Faecal short-chain fatty acids (SCFAs) and bile acids will be quantified in the first week of life (T1), and again four months after probiotic supplementation (T2). Growth parameters, including weight, length, and head circumference, will be assessed at 4 (T2), 12 (T3), and 24 (T4) months of age. Developmental parameters will be evaluated using the Ages and Stages Questionnaire (ASQ) and the ASQ-Social Emotional scale, 2nd version, at 4, 12, and 24 months of age.

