### 3.1. Faecal Sample Collection

Stool samples will be collected from the diaper at two time points in sterile containers from each infant. The first sample (T1) will be collected as soon as possible after birth/admission to the postnatal ward (week 1). The second sample (T2) will be collected at the age of 4 months. All the samples will be labelled, weighed, and stored at −80 °C. After completing recruitment, the samples will be shipped on dry ice to the laboratory for storage at −80 °C and analyses. Acidified samples (5-fold in 1% phosphoric acid) will be shipped on dry ice to the laboratory for SCFA analysis.

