### 3.3. Quantification of SCFA

A modified gas chromatography–mass spectrometry (GC-MS)-based method will be used to extract and analyse SCFAs from the faecal samples. Acetic acid, propionic acid, isobutyric acid, butyric acid, isovaleric acid, 4-methyl valeric acid (internal standard, IS), ethyl acetate, and meta-phosphoric acid will be purchased from Merck (Singapore). For sample preparation, 0.2 g of the faecal sample will be first diluted 5-fold in 1 mL of 1% phosphoric acid and frozen at −20 °C immediately after collection. Before SCFA extraction, the frozen samples will be thawed and added to 100 μL of 10% meta-phosphoric acid solution to adjust the pH to around 2. The samples will be homogenized by vortexing for about 10 min and centrifuged for 30 min at 20,817× *g*. After that, 1 mL of aqueous supernatant will be transferred into a new tube, and 4-methyl valeric acid will be added to achieve a final concentration of 500 μM. Then, the mixture will be vortexed for 30 min and centrifuged for 10 min at 20,817× *g* after addition of 500 μL of ethyl acetate. Then, 2 μL of the organic extracts will be injected in splitless mode into an Agilent GC-MS system (Agilent Technologies (Santa Clara, CA, USA) 7890B-5977B Bundle with Stainless Steel Source) and separated using an HP-FFAP capillary column (30 m × 0.250 mm × 0.25 μm; Agilent, Santa Clara, CA, USA). Helium will be used as the carrier gas at 1 mL/min. The column temperature will initially be 80 °C (1 min), and then increased to 120 °C at 20 °C/min, and finally to 210 °C at 6.13 °C/min and kept at this temperature for 2 min. The solvent delay will be 3.5 min. The detector will be operated in SIM acquisition mode with 30–250 *m/z* range. The injector, ion source, quadrupole, and interface will be set at 250 °C, 230 °C, 150 °C, and 280 °C, respectively. SCFAs will be identified by comparing with the standards and double-confirmed with the NIST 17 library. Quantification will be performed using Mass Hunter Quantitative software (version B.09.00), with base peak ion selected as the quantifier for each SCFA. Calibration graphs will be constructed by plotting relative response (ratio of peak area of SCFA/peak area of IS) versus relative concentration for each SCFA. Final concentrations will be expressed as microgram of SCFA per gram wet weight faecal sample. All analyses will be performed in duplicate. Wilcoxon rank analysis will be performed to compare the SCFA concentrations between the different groups.

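### As listed, the SCFA mixed model has no term for the four-month treatment effect, and a second SCFA test is not ranked against it

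*Protocol article*

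**What the plan says.** Section 2.11 makes faecal SCFA a secondary outcome, measured twice: in the first week of life (T1) and at four months (T2).

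Three statements bear on the analysis:

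- Section 3.7 gives the purpose of the model: "The SCFA data will be analysed using a linear mixed model effect (LME) test to assess the differences between the groups over time".
- The next sentence there lists its terms: "the subjects will be modelled as a random factor, and time and treatment are fixed factors". It names no interaction and no adjustment for T1, and does not say which coefficient carries the treatment test.
- Section 3.3, at the end of the laboratory method, says "Wilcoxon rank analysis will be performed to compare the SCFA concentrations between the different groups". It gives no time point.

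Section 3.7 also has a general rule for continuous data: "Univariate comparisons for the continuous data will be made using the Mann–Whitney test". Nothing in the article says which SCFA result is the main one.

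On timing, section 2.7 has the product "administered from birth till 4 months of age", while section 3.1 has the first stool collected as early as possible in week 1. Neither section says that this sample precedes the first dose.

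**The concern.** With one baseline-type sample and one follow-up sample, the quantity of interest is the arm difference at T2, or the difference in change between arms. A model with only treatment and time as fixed terms forces the arm difference to be the same at both visits. It therefore cannot show how the arms diverge over time, which is its stated purpose. Its treatment coefficient mixes a visit where little or no effect is expected with the visit where the effect should appear.

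The stake is an attenuated SCFA estimate, or a null result read as absence of a metabolic effect. The Discussion gives SCFAs a mechanistic role, so such a reading would matter. An unranked second test on the same data also leaves open which result is to be reported as the finding.

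**Working it through.** **The plan's own figure.** The only power statement is in section 2.9: "A sample size of 30 per group (total 60) was considered adequate to detect a 1.5-fold difference in alpha diversity with 80% power". It concerns alpha diversity, gives no SD, and so cannot be reproduced. Solved backwards with the normal approximation, 30 per arm with 80% power at two-sided 0.05 detects

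d = (1.960 + 0.842) × √(2/30) = 0.723 SD.

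For a 1.5-fold difference this implies an SD on the log scale of ln(1.5)/0.723 = 0.56. I use d = 0.723 only as a benchmark for SCFA. A t-based calculation gives 0.736 and the same rounded powers for the treatment-only term and the T1-adjusted comparison.

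**Inputs**
- From the article: 30 per arm, two-sided 0.05, two SCFA samples per infant.
- Assumed: T2 effect of 0.723 SD, equal variance at both visits, T1–T2 correlation ρ of 0, 0.3 or 0.5, no arm difference at T1, complete pairs.

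**What each analysis estimates.** Let δ1 and δ2 be the arm differences at T1 and T2, in SD units. For two complete visits and a random intercept:

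| Analysis | Estimate | SD factor |
|---|---|---|
| Treatment + time, as listed | (δ1 + δ2)/2 | √((1+ρ)/2) |
| Treatment-by-time term | δ2 − δ1 | √(2(1−ρ)) |
| T2 adjusted for T1 | δ2 − ρδ1 | √(1−ρ²) |

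With δ1 = 0 and δ2 = 0.723, the first row gives 0.362 SD and the other two give 0.723 SD.

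**Power.** Power = Φ(estimate / (SD factor × √(2/30)) − 1.96). At ρ = 0.3:
- As listed: 0.362 / (0.806 × 0.258) = 1.74, power 41%.
- Treatment-by-time: 0.723 / (1.183 × 0.258) = 2.37, power 66%.
- T1-adjusted: 0.723 / (0.954 × 0.258) = 2.94, power 84%.

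| ρ | As listed | Treatment-by-time | T2 adjusted for T1 |
|---|---|---|---|
| 0 | 51% | 51% | 80% |
| 0.3 | 41% | 66% | 84% |
| 0.5 | 37% | 80% | 90% |

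A T2 comparison that ignores T1 has 80% throughout, by construction of d.

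**Simulation check** (300 mixed-model fits, ρ = 0.3). With complete data the treatment coefficient averaged 0.360, a ratio of 0.497 to the true T2 effect, with power 40%. The interaction averaged 0.708 (ratio 0.98), power 64%. With 20% of T2 samples missing at random, the treatment coefficient fell to 0.298 (ratio 0.41), power 29%. The interaction stayed at 0.731 (ratio 1.01), power 63%.

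**Dependence on T1.** If T1 is taken after dosing has begun, δ1 may not be zero. The listed model still reports an average. The table also shows that the interaction then loses δ1 and the T1-adjusted contrast loses ρδ1, so neither alternative is safe unless T1 precedes the first dose.

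**The case against.** The strongest reply is that section 3.7 lists factors rather than a full model formula. It does not exclude an interaction, and its stated aim points towards one. Section 3 adds that the methods are identical to two previous trials, which are not shown, and a condensed article may leave model terms to a fuller document. This stands in part. A reader might infer that a main-effects-only model has been chosen. The text does not say so, and the supportable statement is that the terms it names do not deliver its aim. The article did, however, choose to list the terms, and someone fitting exactly that list would get the averaged coefficient.

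A reader might also infer that the effect is halved as a matter of course. That needs equal arms at T1 and complete pairs. The article guarantees neither.

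It is also tempting to blame the missing interaction for the whole gap of 41% against 84%. Adding that term alone reaches 66% at ρ = 0.3 and gains nothing at ρ = 0. The rest comes from adjusting for T1 rather than subtracting it.

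Lastly, the Wilcoxon rank-sum and Mann–Whitney tests are the same test, so section 3.3 may simply apply the general rule of 3.7. It can coexist with a longitudinal model, and applied at T2 it would not be diluted. That is fair. It does not support a reading that the plan invites selective reporting. What remains is that the time point and the order of the two analyses are not stated.

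**Conclusion.** The point holds in limited form. Fitted as listed, the SCFA model's treatment coefficient is the average of the T1 and T2 arm differences, and it is not the four-month effect whenever those differ. It is about half that effect if the arms are equal at T1 and pairs are complete, and it was lower still (ratio 0.41) when 20% of T2 samples were missing in simulation. The averaging follows from the listed terms and depends on no assumed effect size.

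The power figures are illustrative. They rest on an assumed effect of about 0.72–0.74 SD, assumed correlations and equal variances, none of which the article gives for SCFA. The unranked Wilcoxon comparison in 3.3 is a smaller, separate gap that stands even if an interaction was intended.

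This concerns a secondary outcome and has no bearing on the sample size of 60. It should be corrected before the SCFA data are analysed, but it does not threaten the primary objective.

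**What to change.** In section 3.7, name one main SCFA analysis: the treatment contrast at T2 adjusted for the T1 value. This can be an ANCOVA, or a mixed model with time, treatment-by-time and a common baseline mean for both arms.

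State whether T1 is always taken before the first dose, since sections 2.7 and 3.1 leave this open and the adjustment depends on it. If that cannot be assured, a T2 comparison without T1 adjustment avoids the problem, at 80% power under the assumptions above.

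In section 3.3, give the Wilcoxon comparison a time point and label it supportive, or delete it.

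The cost is two or three sentences and one changed line of model code. No new samples or infants are needed.

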### 2.16. Randomization, Allocation Concealment and Blinding

Group assignment will be allocated by a computer-generated, randomization sequence in randomly ordered block sizes of 2 and 4. Opaque, sealed, coded envelopes will be used for randomization. The neonates of multiple pregnancies will be considered as separate participants. Allocation concealment will be optimized by prescribing allocation only after informed parental consent and recording baseline neonatal data. The clinical trial pharmacist will supply the randomization sequence and sachets (identical design, weight, smell, and taste) containing either the triple-strain Bifidobacteria or placebo (equal volume of dextrin) manufactured by Morinaga Milk Industry Co., Ltd., Tokyo, Japan, to the healthcare personnel looking after the infants on the postnatal wards, and then to the parents. The parents will be educated about reconstituting the sachets and administering the probiotic or placebo at home and to monitor for any adverse effects. The hospital pharmacy will supply additional sachets to parents of participating infants as needed till the completion of the protocol (4 months of age). This will assure the masking of all investigators, clinical and non-clinical outcome assessors, midwifery and nursing staff, and the parents with regarding to the allocation of the enrolled infants.

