## 5. Conclusions

We believe our innovative trial assessing the effects of probiotic supplementation on dysbiosis in the infants of mothers with GDM will provide robust data on gut microbiota, faecal short-chain fatty acids, long-term growth, and neurodevelopmental outcomes to guide adequately powered robust RCTs in this field.

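### Section 3.7 calls every test with p<0.05 significant; across the 15 or more secondary growth and ASQ comparisons this materially inflates the chance of a false significant finding, to about 20–54%

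*Protocol article*

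**What the plan says.** The decision rule is in section 3.7, whose title covers clinical, SCFA, bile-acid and microbiome data: "All the tests will be two-sided, and a *p*-value < 0.05 will be considered significant". The sentence does not distinguish primary from secondary outcomes.

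The outcomes it reaches are in section 2.11. For growth: "Growth parameters, including weight, length, and head circumference, will be assessed at 4 (T2), 12 (T3), and 24 (T4) months of age". For development: "Developmental parameters will be evaluated using the Ages and Stages Questionnaire (ASQ) and the ASQ-Social Emotional scale, 2nd version, at 4, 12, and 24 months". The same section adds faecal SCFAs and bile acids at the first week and at four months. Section 3.3 names five SCFA analytes besides the internal standard.

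Section 3.7 assigns the Mann–Whitney test to continuous data and the chi-square or Fisher test to categorical data. Only SCFAs are given a model over time.

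The sample size in section 2.9, 30 infants per group, rests on alpha diversity alone; its stated aim is "to detect a 1.5-fold difference in alpha diversity with 80% power and a significance level of 0.05".

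The Conclusions say the trial "will provide robust data on gut microbiota, faecal short-chain fatty acids, long-term growth, and neurodevelopmental outcomes". The same sentence goes on to say that these data are meant to inform later, adequately powered trials.

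**The concern.** A flat rule applied to many secondary comparisons gives an inert product several chances to produce a result that the plan itself labels significant. The protocol's own background makes no effect on growth or development a realistic possibility. Section 2.13 cites a review of nine trials (3026 participants) that found no neurocognitive difference except in a subgroup treated for more than six months; here treatment lasts four. It also cites a review of 79 trials that found a possible small effect on weight and height in low- and middle-income countries but not in high-income ones; this trial is in Western Australia.

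The trial is also small for these outcomes. With 30 infants per group, a result reaches p<0.05 only if the observed difference is about half a standard deviation (shown in the working). A chance finding would therefore look large. The difficulty runs both ways: an isolated unfavourable difference in, say, head circumference at one age would be just as hard to interpret as a favourable one.

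**Working it through.** **The plan's own figure.** The plan gives no familywise error rate for the secondary outcomes, so there is none to reproduce. Its one design figure, 30 per group for a 1.5-fold difference in alpha diversity, cannot be reproduced either, because no standard deviation is given. On the log scale, 30 per group detects (1.960 + 0.842) × √(2/30) = 0.723 SD with 80% power, so a 1.5-fold difference fits only if the SD is ln(1.5)/0.723 = 0.405/0.723 ≈ 0.56. This has no bearing on the point made here.

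**Number of tests.**
- Growth (section 2.11): 3 measures × 3 ages = 9.
- ASQ (section 2.11): 2 instruments × 3 ages = 6, assuming one score per instrument.
- Growth plus ASQ: 15.
- SCFAs (section 3.3): 5 analytes, giving 20.
- Bile acids: counted as one test, giving 21. The documents fix no number.

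The count assumes a separate comparison at each age. Section 3.7 suggests this, since it offers only univariate tests for these outcomes, but does not say it outright. Scoring the ASQ by domain, testing within the three pre-planned subgroups, or using both SCFA tests (Wilcoxon in 3.3, mixed model in 3.7) would add tests. None of these is counted.

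**Independent tests.** P(at least one p<0.05) = 1 − 0.95^k.
- k = 9: 1 − 0.630 = 37.0%
- k = 6: 1 − 0.735 = 26.5%
- k = 15: 1 − 0.463 = 53.7%

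The expected number of false positives among 15 tests is 15 × 0.05 = 0.75, whatever the correlation.

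**Correlated tests.** Repeated measurements on the same infants are correlated, and the documents give no values, so a range is assumed. Test statistics were simulated as multivariate normal with a common correlation (400,000 draws), two-sided at 0.05:

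| Tests | 0 | 0.3 | 0.5 | 0.7 | 0.8 | 0.9 |
|---|---|---|---|---|---|---|
| 9 (growth) | 37.0% | 32.7% | 26.9% | 20.3% | 16.5% | 12.4% |
| 15 (growth + ASQ) | 53.7% | 45.6% | 36.2% | 25.5% | 20.1% | 14.3% |
| 21 (+ SCFAs, one bile-acid test) | 65.9% | 55.6% | 42.9% | 29.5% | 22.8% | 15.6% |

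In a second structure, growth and ASQ are independent of each other. Within each block the same correlation applies between measures and between ages, and is multiplied where both differ. The 15 tests then give 50.4%, 44.8%, 36.3% and 30.7% at correlations of 0.3, 0.5, 0.7 and 0.8.

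**Check on the per-test level.** A simulated Mann–Whitney test with 30 per group rejected a true null 4.9% of the time, so 5% per test is a fair approximation for continuous outcomes.

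**Size of a chance finding.** At 30 per group, p<0.05 needs an observed difference of about 1.96 × √(2/30) = 0.51 SD (normal approximation).

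**The case against.** The strongest reply is that this is a condensed journal article, and that the handling of multiplicity among secondary outcomes is commonly left to an analysis plan, which is not shown. That is right as far as it goes: the lack of a testing order, a key secondary outcome or an alpha split is not a fault here. But section 3.7 is not silent. It states a rule that covers every test, and an analysis plan that treated the secondary outcomes as exploratory would sit at odds with it.

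It can also be said that growth and development are plainly labelled secondary, that the hypothesis and primary objective concern dysbiosis only, and that unadjusted secondary tests are ordinary when presented as supportive. All of this stands. It lowers the weight of the point, but the secondary label does not narrow the rule in 3.7.

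The test structure is partly inferred. The article does not say whether the ASQ is analysed as a score or a category. If it is categorised, Fisher's exact test is conservative in small samples and the figures would be somewhat lower.

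Three stronger readings are tempting and are not supported:
- A reader might infer that a false growth or developmental finding is more likely than not. For the 15 tests that holds only near independence, which is implausible for weight, length and head circumference measured repeatedly in the same infants.
- A reader might set 20–54% against the stated 5% and call it a four- to eleven-fold breach. The 5% is a per-test level; the plan claims no familywise rate, so the two are not like for like.
- A reader might take the Conclusions as announcing confirmatory growth and neurodevelopment claims. Read to its end, the sentence offers the data as a guide to later trials. That a chance difference would be reported as a treatment effect is a prediction, not something the plan says.

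**Conclusion.** The point holds as a cheap and worthwhile improvement, not as a threat to the primary result. Followed as written, section 3.7 would label as significant any of at least 15 growth and ASQ comparisons that reaches p<0.05. With no true effect, the chance of at least one such label is about 36% at a common correlation of 0.5, and 20% to 54% for correlations from 0.8 down to zero. Even at 0.9 it is 14%.

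These figures rest on one score per ASQ instrument, a separate comparison at each age, tests of about 5% size, and assumed correlations. SCFAs and bile acids widen the family that the rule covers but add nothing to the chance of a false growth or ASQ result. Low power for the secondary outcomes does not raise the false-positive rate either; it only means that a chance finding will look large. The multiplicity of the primary microbiome variables in section 2.10 is a separate matter.

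**What to change.** In section 3.7, limit the p<0.05 significance rule to the primary comparison and add a sentence such as: *Growth, ASQ, SCFA and bile-acid results will be reported as estimates with 95% confidence intervals; any p-values are not adjusted for multiplicity and are hypothesis-generating.* Alongside the Mann–Whitney test, a Hodges–Lehmann shift estimate with its interval would serve.

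In the Conclusions, describe the growth and neurodevelopment data as exploratory estimates. This agrees with the purpose that the sentence already gives them.

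The cost is wording only, with no extra infants or data. The downside is that an isolated secondary p<0.05 can no longer be called significant. Formal adjustment is not needed: Bonferroni over 15 tests would require p<0.0033 and raise the difference detectable with 80% power at 30 per group from 0.72 to 0.98 SD. Naming one key secondary measure and age in advance, or analysing the three ages in a repeated-measures model, is optional, and statisticians differ on both.
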